#### Concealment mechanism {16b}

A computer-generated randomisation sequence will be used to allocate schools into the intervention and wait-list control arms of the trial. The research team will not be fully blinded to the group allocation. Schools will be informed of which group they have been allocated to and therefore the schools will not be blind to their allocation.

#### Implementation {16c}

The lead researcher (KV) will enrol participants in the study and allocate them a unique ID number. One member of the research team (CE), blinded to the schools, will generate the allocation sequence using the school ID numbers but not the school names. The lead researcher (KV) will then inform schools which group they have been allocated to.

### Assignment of interventions: blinding

#### Who will be blinded {17a}

There will be full blinding at T1 baseline data collection by trial participants, schools and the research team, since randomisation will take place after data is collected. This is a pragmatic trial evaluating the effectiveness of a food skills-based intervention and therefore it is not possible for trial participants, schools or parents to be blinded after assignment to the intervention groups. We plan for the blinding of outcome assessors at T2 by using additional research team members from the University of Leeds to undertake data collection in the participating schools. This will be dependent on access to further funding being sought. It will not be possible for the data analyst to be blinded, since this work is in support of a PhD thesis by the main author of the study.

#### Procedure for unblinding if needed {17b}

N/A—no procedure for unblinding as part of this trial as participants are not blinded to the allocated group.

### Data collection and management

#### Plans for assessment and collection of outcomes {18a}

Data collection will be via paper surveys at two time points: baseline (T1) and 12 months post-intervention (T2). The two child surveys on Food Literacy and Cooking Skills will be conducted on the school premises in a whole class setting. The fruit and veg diet diary (CADET) will be sent home to parents in paper format, asking them to complete it and send it back to the school.

#### Plans to promote participant retention and complete follow-up {18b}

Short articles about the research project will be sent out in School Newsletters in the half-term before data collection with a photograph of the main researcher (KV) to make the message more personal. It is hoped that this personal approach will encourage the completion of the CADET fruit and veg survey by parents.

#### Data management {19}

All paper-based data will be collected by the lead researcher and held in locked filing cabinets in a locked office. There will need to be some training undertaken for the coding work on diaries and questionnaires to ensure a consistent approach across the research team. For data entry, a 5% sample will be checked by another member of the research team to monitor error rates. The data will be inputted into MS EXCEL by the lead researcher (KV), exported to SPSS and STATA for analysis and saved on the University of Leeds SAN (Storage Area Network), which comprises enterprise-level disk storage and file servers located in physically secure data centres with appropriate fire suppression equipment. The electronic data will be accessible only to the research team.

#### Confidentiality {27}

Individual participants will be given an anonymous unique identity number. All participating schools and families will be informed that the data provided will be treated confidentially. It will be explained that the research team are the only people who will look at the data and that the published reports of results will not identify any individuals either before, during or after the trial.

#### Plans for collection, laboratory evaluation and storage of biological specimens for genetic or molecular analysis in this trial/future use {33}

N/A—no biological specimens are collected as part of this trial.

## Statistical methods

### Statistical methods for primary and secondary outcomes {20a}

Baseline demographic characteristics for the participating schools will be summarised using means and 95% confidence intervals for continuous variables and frequencies and percentages for categorical variables. Contextual data such as %FSM eligibility, IMD and Public Health England data from National Child Measurement Programme (NCMP) [1] will be provided at school and Lower Super Output Area (LSOA) [20] levels respectively in a summary table.

Primary analysis of the effectiveness of the intervention on outcome data for the trial arms will be compared using two-way mixed analysis of variance (ANOVA) and multivariable regression models. The statistical analyses will be conducted using the following: food literacy score, cooking skills score and fruit and vegetable intake score as the dependent variables; time (T1 and T2) as the repeated measures independent variable; and treatment (intervention/control) as the independent groups variable. Effect size coefficients will be reported with measures of variation as well as Cohen’s *d* to determine the relative size of the effectiveness. We have identified the key outcomes on which we are basing our evaluation and any additional results will be interpreted cautiously and with the awareness that multiple testing is an issue. To reduce this risk, we will consider using statistical significance at the 1% level.

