**Methods:**

A cluster randomised controlled trial will be undertaken in 28 primary schools in North Yorkshire, UK, including a total population of children aged 7–9 years (*n* = 420). The trial has two arms: (a) the intervention group receiving PhunkyFoods programme (*n* = 210) and (b) the wait-list control group receiving the usual school curriculum (*n* = 210). The intervention ‘PhunkyFoods’ will be delivered by Purely Nutrition Ltd. The participating school staff are supported with training, policy development and access to resources to improve the delivery of nutrition education. Children participate through whole school assemblies, classroom activities, and after-school clubs about food preparation, cooking healthy meals and healthy living. Schools, parents and children have access to healthy meal recipes through the PhunkyFoods website. The primary outcomes are differences in food literacy and cooking skills scores between control and intervention arms after 12 months of the intervention and adjusted for baseline values. The secondary outcome is differences in fruit and vegetable intake between the arms after 12 months (adjusted for baseline). Treatment effects will be examined using mixed ANOVA and regression analysis. Primary analyses will adjust for baseline food literacy and cooking skills scores and secondary analysis will adjust for pre-specified baseline school and child level covariates.

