### Trial design {8}

The PhunkyFoods evaluation design is a parallel, cluster randomised controlled trial, with two arms and with a 1:1 allocation ratio. The intervention arm will receive the PhunkyFoods programme starting in May 2022, and the wait-list control arm will receive the PhunkyFoods programme after the final research data collection, with training from May 2023 (superiority trial). If the trial is not able to recruit 28 schools within the recruitment period, then the research team will consider an unequal allocation ratio with a smaller number of schools in the control group or widening the geographical recruitment area. The impact of this is discussed in the section on sample size.

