#### Sample size {14}

The study by Dean and colleagues in 2019, based on 469 participants and using CooC11 to assess cooking competence, showed a significant increase (*p* < 0.01) in cooking competence at follow-up after the camp-based intervention compared with results at baseline [15]. The results of CooC11 at baseline (mean (SD)) were 21.75 (7.89) and at follow-up 26.13 (8.89). The difference in cooking competence scores was therefore approximately 5 units, the equivalent of a moderate effect size (Cohen’s *d* = 0.52).

A power calculation was undertaken using STATA based on this moderate effect size of the Dean study. To detect this effect size with a minimum of 90% power and using a 2-level model with individuals clustered within schools (individual schools are being recruited rather than individual children), 13 clusters are needed in each arm. This calculation was based on the assumption that a mean of 15 children would be included in each school, and therefore, 195 children would be needed in each arm. The power is reduced when a large proportion of variation is at the school level (most of the variation will be at the individual level); in other words, children within a school may be more similar to each other than children at another school and therefore a conservative estimate of 20% of variation at the school level was assumed. It is likely that it is less than this, but there is too little information available related to cooking competence to be able to estimate it with more certainty. Due to the reasonable possibility that schools may drop out of the study, we aim to recruit 14 schools per arm (28 schools in total).

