### Assignment of interventions: allocation

#### Sequence generation {16a}

A computer-generated randomisation sequence will be used to allocate schools into the intervention and wait-list control arms of the trial. Block randomisation will be used to ensure equivalence between intervention and waitlist-control schools. Furthermore, schools will be stratified according to region (e.g. Selby or Harrogate) and whether they are above or below the England median for free school meals eligibility [19]. The randomisation will be conducted immediately after T1 baseline data is collected.

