### Methods for additional analyses (e.g. subgroup analyses) {20b}

Secondary analysis will use a theory-based approach to explore the interplay of mechanisms and context [10], including model fidelity. This will involve adjusting for pre-specified baseline school and child level covariates to investigate the impact of the intervention arm for individual clusters. Multiple regression will be used with the number of intervention components as a predictor variable. In addition, %FSM and IMD will be used in a linear model as predictor variables. The study will have low power to detect all but the largest differences in subgroups.

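### The stated primary analysis has no school term, although schools are randomised and the sample size assumes a two-level model

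*Protocol article*

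**What the plan says.** Trial design {8} describes a "parallel, cluster randomised controlled trial, with two arms and with a 1:1 allocation ratio". Sequence generation {16a} makes the school the unit: "A computer-generated randomisation sequence will be used to allocate schools into the intervention and wait-list control arms of the trial". Sample size {14} says that power was calculated "using a 2-level model with individuals clustered within schools", with 15 children per school on average, and that "a conservative estimate of 20% of variation at the school level was assumed". It adds that the true share is probably lower.

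Statistical methods {20a} says the effects on outcome in the two arms "will be compared using two-way mixed analysis of variance (ANOVA) and multivariable regression models". For food literacy, cooking skills and fruit and vegetable intake alike, the factors it names are "time (T1 and T2) as the repeated measures independent variable; and treatment (intervention/control) as the independent groups variable". The abstract adds one element: "Primary analyses will adjust for baseline food literacy and cooking skills scores".

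School-level variables otherwise enter as covariates or predictors, chiefly in the additional analyses {20b}, where "Multiple regression will be used with the number of intervention components as a predictor variable". No section states a random effect for school, a cluster-robust standard error or an analysis of school means.

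**The concern.** With time as the repeated factor and treatment as the group factor, the word mixed in {20a} means one within-child and one between-group factor. It does not mean a random effect for school. The error term for treatment is then built from children, whereas the quantity that was randomised is the school.

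If children in a school resemble each other, as {14} says they may, the information on the treatment effect is overstated. P-values become too small and confidence intervals too narrow. Both primary outcomes and the secondary outcome are affected, and a programme with no effect could be declared effective. The stated analysis also drops the structure on which the sample size rests.

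**Working it through.** **Inputs.** From {14}: ICC 0.20, m = 15 children per school, 14 schools per arm recruited (13 needed), d = 0.52, power 90%. Assumed: two-sided 5% for the power calculation, because {14} gives no level. {20a} only considers 1%.

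**1. The plan's own figures.** The effect size reproduces: (26.13 − 21.75) / pooled SD 8.40 = 4.38 / 8.40 = 0.52. The design effect from the stated inputs is 1 + (15 − 1) × 0.20 = 3.8. The 13 schools per arm do not reproduce: d = 0.52 needs 78 children per arm without clustering, and 78 × 3.8 / 15 = 19.8, so 20 schools. An ICC of 0.10 would give 78 × 2.4 / 15 = 12.5, so 13; a baseline correlation of about 0.6 would also give 13. That is a separate matter. What counts here is that {14} intends clustering to be in the model.

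**2. A child-level comparison of scores without school.** The standard error is too small by √DE, with DE = 1 + 14 × ICC. The false-positive rate is 2 × [1 − Φ(z / √DE)], with z = 1.96 (5%) or 2.576 (1%).

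| ICC | DE | √DE | nominal 5% | nominal 1% |
|---|---|---|---|---|
| 0.20 | 3.80 | 1.95 | 31.5% | 18.6% |
| 0.10 | 2.40 | 1.55 | 20.6% | 9.6% |
| 0.05 | 1.70 | 1.30 | 13.3% | 4.8% |
| 0.01 | 1.14 | 1.07 | 6.6% | 1.6% |

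**3. The time-by-treatment interaction.** This test compares changes from T1 to T2, so only school variation in change inflates it. Let c be the correlation of school effects between the two waves and r the child-level correlation. Both are assumptions, as the article gives neither. The ICC of the change score is ICC(1 − c) / [ICC(1 − c) + (1 − ICC)(1 − r)], which then goes into the formula of step 2. With r = 0.5 and a nominal 5%:

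| ICC | c = 0.5 | c = 0.8 | c = 0.9 | c = 1 |
|---|---|---|---|---|
| 0.20 | 31.5% | 19.4% | 12.9% | 5% |
| 0.10 | 20.6% | 12.1% | 8.6% | 5% |
| 0.05 | 13.3% | 8.4% | 6.7% | 5% |

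Example, ICC 0.20 and c = 0.9: 0.02 / (0.02 + 0.40) = 0.048; DE = 1 + 14 × 0.048 = 1.67; rate 12.9%. Simulation of 14 + 14 schools of 15 children agreed: about 13% to 32% at ICC 0.20 for c from 0.9 to 0.5.

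**4. Child-level regression on baseline, without school.** Simulated at ICC 0.20 and r = 0.5, the rate was 31%, 22%, 19% and 13% for c = 0.5, 0.8, 0.9 and 1. Baseline adjustment alone does not remove the problem, even with fully stable school effects.

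**5. Analyses that respect the school.** In simulation, school-mean ANCOVA rejected a true null in 4.8% to 5.7% of runs, and school-mean change (28 units, 26 df) in 4.7% to 5.7%. The mixed model proposed below was not itself simulated.

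**The case against.** The strongest reply is that the article is condensed. The authors plainly know about clustering, since {14} describes it, and the factor list in {20a} is not complete: the abstract's baseline adjustment is missing from it. The regression models are named without their error structure and could carry a school effect. A reader might therefore infer too much in saying that every primary p-value will ignore clustering; the documents do not establish that. What stands is narrower. The mixed ANOVA, with the factors stated, has no place for school, and nothing carries the two-level model of {14} into the analysis. This is not a detail left to a later plan, because the article names the method and its factors. It also says the analyst will not be blinded {17a}, which is a reason to fix the model in advance.

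A second reply concerns size, and it largely holds. A reader might infer that the error rate is several times 5% whatever the circumstances. The text does not support that: {14} calls 20% conservative and expects less, and the interaction test is inflated only by school variation in change. At ICC 0.05 with c = 0.9 and r = 0.5 its rate is about 7%.

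Third, a reader might infer that the component-count regression in {20b} has the same fault. Its unit of analysis is not stated, and because the predictor is a count per school, a school-level regression would fit the wording.

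Finally, the 1% level is no safeguard. It is only to be considered, and it is offered against multiple testing. At ICC 0.20 a nominal 1% child-level test still rejects a true null about 19% of the time.

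**Conclusion.** The point holds for {20a} set against {8}, {16a} and {14}: the stated primary analysis omits the unit of randomisation and contradicts the model behind the sample size. As written, its standard errors are too small. How far too small is conditional. The 31% figure belongs to a child-level comparison at the protocol's own ICC and cluster size, and it falls to about 7% at ICC 0.01. The 13% to 32% range for the interaction rests on ICC 0.20 and on assumed correlations (school effects 0.9 to 0.5 between waves, children 0.5); with fully stable school effects that test is near 5%. Since the ICC is admittedly uncertain and the stability of school effects is unknown, the plan cannot rely on the favourable case. This must be corrected before analysis.

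**What to change.** Replace the mixed ANOVA as primary analysis by a linear mixed model for the T2 score. Fixed effects: arm and the baseline score of the same outcome, which the abstract already requires, and preferably the stratification factors of {16a} (region, and free-school-meal eligibility above or below the national median). Add a random intercept for school, with Kenward-Roger or Satterthwaite degrees of freedom because there are only 28 schools. An equivalent school-level ANCOVA is an acceptable alternative; one of the two should be named as primary. Apply it to TFLAC, CooC11 and CADET, and report the estimated ICCs. Say in {20b} that any secondary regression run on children carries the same school effect.

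The change is one of wording. It needs no new data, and STATA is already planned in Data management {19}. The cost is wider, correct confidence intervals. The authors should expect this to show in the power: at d = 0.52 and ICC 0.20, 14 schools per arm give about 78% (normal approximation) or 75% (t), before any gain from baseline adjustment.

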### Methods in analysis to handle protocol non-adherence and any statistical methods to handle missing data {20c}

Missing data will be reported and associations between outcomes considered. A sensitivity analysis will be undertaken if deemed appropriate, depending on the extent of the missing data.

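### Two non-equivalent primary methods are named without choosing one, and the only model terms listed leave out the promised baseline covariate

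*Protocol article*

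**What the plan says.** The Methods paragraph of the abstract defines the primary outcomes as "differences in food literacy and cooking skills scores between control and intervention arms after 12 months of the intervention and adjusted for baseline values". It then says "Treatment effects will be examined using mixed ANOVA and regression analysis" and "Primary analyses will adjust for baseline food literacy and cooking skills scores".

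Section {20a} of the protocol article says the primary analysis of the outcome data "will be compared using two-way mixed analysis of variance (ANOVA) and multivariable regression models". It goes on to list model terms: each score as the dependent variable, "time (T1 and T2) as the repeated measures independent variable; and treatment (intervention/control) as the independent groups variable". It lists no baseline covariate, does not say which of the two methods is primary, and does not say which term carries the treatment effect. Section {20b} places adjustment for pre-specified school and child baseline covariates in the secondary analysis.

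**The concern.** In the terms listed in {20a} the T1 score is one level of the outcome, whereas the abstract treats it as something to adjust for. These are different analyses and will generally give different estimates, standard errors and p-values from the same data.

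Two things are at stake. The first is precision: in a trial of 28 schools, the analysis that the listed terms describe makes poorer use of the baseline scores than the one the abstract promises. The second is an open choice. Section {17a} says the data analyst cannot be blinded. With two methods under the primary heading and neither designated, the choice of headline result could be made after the results by arm are known.

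**Working it through.** **1. What the listed terms test.** With two waves and two arms, the time-by-treatment F statistic equals the squared t statistic comparing mean change between arms. A numerical check on simulated data gave 11.285 for both. So the part of the mixed ANOVA that isolates the treatment effect is a change-score comparison.

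**2. Variance of the two estimators.** Let s1 and s2 be the SDs at T1 and T2, and r the correlation between waves.
- Change score: s1² + s2² − 2·r·s1·s2
- ANCOVA: s2²(1 − r²)
- Difference: (s1 − r·s2)², which is never negative

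With equal SDs these become 2(1 − r) and 1 − r², in units of the T2 variance, and their ratio is 2/(1 + r).

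**3. Inputs.** The protocol gives no 12-month correlation, so r = 0.3 to 0.8 is an assumption. The Primary outcome measures section reports a temporal stability of 0.91 for CooC11 and intraclass correlations of 0.64 to 0.70 for TFLAC. These are reliability figures and at best upper guides to a 12-month correlation. The only pre/post SDs, 7.89 and 8.89, come from the single-group camp study cited in section {14}. With them the change-score variance is 62.25 + 79.03 − 140.28r and the ANCOVA variance is 79.03(1 − r²).

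| r (assumed) | Change/ANCOVA variance, equal SDs | Same, SDs 7.89 and 8.89 |
|---|---|---|
| 0.3 | 2/1.3 = 1.54 | 99.20/71.92 = 1.38 |
| 0.5 | 2/1.5 = 1.33 | 71.14/59.27 = 1.20 |
| 0.6 | 2/1.6 = 1.25 | 57.11/50.58 = 1.13 |
| 0.7 | 2/1.7 = 1.18 | 43.09/40.31 = 1.07 |
| 0.8 | 2/1.8 = 1.11 | 29.06/28.45 = 1.02 |

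Read as a saving from using ANCOVA, the last column is about 17% at r = 0.5 (1 − 1/1.20) and 11% at r = 0.6 (1 − 1/1.13).

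**4. The same comparison with clustering.** In a simulation of 14 + 14 schools of 15 children, with 20% of variance at school level, child-level correlation 0.5 and equal SDs, ANCOVA on school means had 7% to 21% less variance than change scores. The saving was 7% at a between-wave school correlation of 0.9 and 21% at 0.5.

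**5. In terms of power.** Section {14} uses d = 0.52, which follows from (26.13 − 21.75)/8.40 = 0.521, where 8.40 is the pooled SD √((7.89² + 8.89²)/2). It also uses 13 schools per arm, 15 children per school (195 per arm) and a 20% school share, so the design effect is 1 + 14 × 0.20 = 3.8. I assume two-sided 5%, equal SDs and the same r at child and school level. The standard error is √(2 × 3.8 × f/195), with f = 1 − r² for ANCOVA and f = 2(1 − r) for change.

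| r | ANCOVA power | Change-score power |
|---|---|---|
| 0.3 | 79% | 61% |
| 0.5 | 86% | 75% |
| 0.7 | 96% | 93% |
| 0.8 | 99% | 99% |

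A T2-only comparison (f = 1) gives 75% on these inputs. The stated 90% is therefore not reproduced; two-sided 5% would need 19.7 schools per arm. That is a separate matter, and the table is meant only to compare the two methods.

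**The case against.** The strongest reply is that {20a} names multivariable regression alongside the ANOVA, and a regression can carry the T1 score. The abstract also names mixed ANOVA. So a reader who infers that the abstract promises one analysis and the methods section another goes too far: both places name the same two methods. It can be added that a separate analysis plan may settle the model. What remains is that neither place designates one method, and that the terms the protocol does list fit only the ANOVA. This is a stated specification that does not deliver the promised adjustment, so it is more than detail left for later.

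Three stronger readings are tempting, and the document does not support them.

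- **The ANOVA loses children who miss a wave, and the alternative would not.** A classical mixed ANOVA does lose them, but a complete-case regression on the T1 score loses the same children. Section {20c} states no complete-case rule; it says only "A sensitivity analysis will be undertaken if deemed appropriate, depending on the extent of the missing data".
- **Chance baseline imbalance is left in place.** Change scores subtract the whole baseline difference, so with similar SDs and r below 1 they over-correct a chance imbalance. Both estimators are unbiased over randomisation.
- **The plan tests the treatment main effect, which averages T1 with T2 and so estimates half the 12-month effect.** Section {20a} names no test term, so this is a possible misreading and not a stated plan.

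It is also fair that the loss becomes small when r is high.

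**Conclusion.** The point holds as one of precision and of an unfixed primary model; it is not one of bias. The abstract and {20a} name two non-equivalent methods without choosing between them, and the listed terms omit the baseline covariate that the abstract promises.

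If the mixed ANOVA were used, its variance would exceed that of ANCOVA by about 54% at r = 0.3, falling to 11% at r = 0.8, with equal SDs. With the cited study's SDs the excess is about 38% falling to 2%. The range rests on an assumed correlation, and the second set of figures also on SDs from an uncontrolled study of a different intervention. That the change-score test is never more precise than ANCOVA in these large-sample formulas does not depend on those assumptions. The change is worth making because it is specific and uses data the trial already collects.

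**What to change.** In section {20a}, designate one primary model for each outcome: T2 score on arm, with the child's own T1 score as covariate and a random intercept for school. An acceptable alternative is a constrained-baseline linear mixed model with school effects, which also keeps children seen at only one wave. State that the primary estimate is the adjusted mean difference at T2.

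Remove the two-way mixed ANOVA, or keep it as a supporting analysis with the time-by-treatment term named as its contrast. Align the abstract, and any separate analysis plan, with that choice before the T2 data are examined by arm. No further data are needed; the cost is a change of wording.
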